### 3.5 Sample Size Determination

The total sample size including the Phases I, II, and III is estimated a minimum of 450 pediatric, adolescent and adult patient venous and capillary WB specimens, from the study site that provide valid results (i.e. meeting enrollment and protocol testing criteria) will be required for the three phases of the study. The selection of samples for this study will follow a convenience sampling method, and will

include representatives at both extremes of the 95% CI for CD4 and Hb parameters. The projected number of samples, as detailed below for each phase of the study, is in accordance with and exceeds the revised CLSI guidelines for method comparison so as to increase the power of subsequent analyses.

- I. **Feasibility Phase:** A minimum of 200 venous and 200 capillary specimens.
- II. **External Customer Evaluation:** A minimum of 50 venous and 50 capillary blood specimens.
- III. **Regulatory submission for CE-IVD and US FDA 510K Submission for market clearance Evaluation:** A minimum of 400 venous and 400 capillary blood specimens from three or more sites.

#### 4.0 ACCURACY STUDY GENERAL METHODS AND PROCEDURES

These procedures are replicable in other phases of the study. Details for every phase are already provided in this protocol.

##### 4.1 Daily Study Activities

Daily study activities include the following:

- Subject and specimen enrollment
- Instrument set-up and Process Controls
- Sample Preparation and Testing, and
- Data review, Compilation and daily update to BD
- Weekly submission of the data to BD

###### 4.1.1 Subject Enrollment

On each day of study testing, the Study site staff will inquire to the HIV/AIDS patients attending for flow cytometry lymphocyte subset evaluation (CD4 testing) routine testing if they would be willing to participate in the study and donate blood. The subjects willing to participate in the study will be evaluated for inclusion. If all inclusion criteria are met and none of the exclusion criteria are positive the subject will undergo the informed consent process and provide written informed consent prior to any study-related blood draw. Designated site staff (i.e. study coordinator) will pre-screen the subject's medical records to compile and identify the previous CD4 absolute counts and percentage CD4 results for CD4/Hb bin placement and whether may satisfy the study age and CD4/Hb bin requirements (see sections 5.2.1 and 5.2.2).

Then, subject's venous blood will be drawn according to the facility phlebotomy procedures. Capillary blood will be collected following procedure shown in Appendix 2.

All specimens enrolled in the study will be de-identified from the patient's personal health information by the assignment of a study-specific specimen ID prior to study testing. Guidelines for target enrollment populations are detailed in Section 5.2.1 and 5.2.2.

During the enrollment process, specimen information will be documented on Case Report Forms (CRFs). In addition to documenting that inclusion criteria have been met, the following patient demographic data will be captured:

- Patient's age (for bin assignment)
- Patient's gender
- Specimen collection date and time
- The hand (left or right) used for capillary blood collection
- Relevant co-morbid conditions: Anemia, Sickle Cell Anemia, Tuberculosis, Malaria, Thalassemia, Infections, other medical conditions
- Relevant medications: ART, antimalaria, antituberculosis, other

The information that is brought forward from diagnostic specimen identification during study enrollment will be considered to be source documentation once transferred to the CRF, and there will be no re-linking performed to verify the accuracy of this data against diagnostic records.

**Figure 1: Venous and Capillary Blood Testing**

[figure not shown]

#### 4.1.2 Venous Blood Specimen

Venous blood specimen enrollment will involve:

- Patient provided written informed consent.
- Evaluation of specimens for enrollment based on inclusion/exclusion criteria.
- Collecting demographic information.
- De-linking the existing specimen ID by assigning a study-specific specimen ID to the aliquot/specimen tube and all applicable study documentation
- Completion of Case Report Form(s) (CRFs) and any additionally required logs.

Phlebotomy will be performed by an experienced clinical staff, to draw about 2 ml of blood for the study procedures.

#### 4.1.3 Capillary Blood Collection

Capillary blood collection will be done according to the site approved standard procedures and CLSI H04-A6 and the method of capillary blood collection depicted on appendix 9 of this protocol

Overview

- Ensure subject has willingly provided written informed consent
- Prepare supplies and subject for capillary blood collection
- Apply the methods described in Appendix 2
- Transfer blood to the PEO/IUO BD CD4/%CD4/Hb cartridges, by positioning the cartridge directly beneath the puncture site.
- Ensure blood flows through the channel
- Lock the PEO/IUO BD cartridge cap.

Ensure subject's safety by monitoring hemostasis before releasing the subject.

#### 4.1.4 Enrollment by Subjects Age

A minimum of 400 valid AbsCD4 results are required to be collected in four age groups, the anticipated number patients enrolled by age is as follows:

| Group    | Patient Age     | Anticipated |
|----------|-----------------|-------------|
| Children | 0-12 years old  | 80          |
| Young    | 13-25 years old | 100         |
| Mid      | 26-50 years old | 160         |
| Older    | > 51 years old  | 60          |

#### 4.1.5 Enrollment by CD4 Count

Enrollment by AbsCD4 and %CD4 binning will be done using the first replicate of the predicate results. If diagnostic CD4 counts are available at the time of specimen enrollment, site should enroll an approximately equal number of specimens in each CD4+ absolute count, %CD4 bins as shown in the following tables (specimens can be from any age):

**Abs CD4 Bins for Accuracy**

| AbsCD4 | Bins (cells/ <math>\mu</math>L) | Total # Desired | Minimum |
|---------------|----------------------------------------|------------------------|----------------|
|               | 1) $50 \leq \text{CD4} < 250$          | 100                    | 80             |
|               | 2) $250 \leq \text{CD4} < 500$         | 100                    | 80             |
|               | 3) $500 \leq \text{CD4} < 1000$        | 100                    | 80             |
|               | 4) $1000 \leq \text{CD4} \leq 5000$    | 100                    | 80             |
| %CD4   | Bins (%CD4)                     | Total # Desired | min     |
|               | 1) $5 \leq \text{CD4\%} < 20\%$        | 133                    | 110            |
|               | 2) $20 \leq \text{CD4\%} < 35\%$       | 134                    | 110            |
|               | 3) $35 \leq \text{CD4\%} \leq 65\%$    | 133                    | 110            |

**4.1.6 Enrollment by Hb (only venous blood)**

For Hb binning assignment will be done using the first replicate from the predicate method (Sysmex KX-21), Hb enrollment will follow the binning shown below.

**Hb Bins for Accuracy**

| Bins (g/dL)          | Anticipated total | Max-min |
|-----------------------------|--------------------------|----------------|
| 1) $2 \leq \text{Hb} < 9$   | 140                      | 90             |
| 2) $9 \leq \text{Hb} < 13$  | 180                      | 100            |
| 3) $13 \leq \text{Hb} < 20$ | 80                       | 60             |

**Clinical decision points for Hb (only capillary blood)**

| Bins (g/dL) | Anticipated total | Minimum |
|--------------------|--------------------------|----------------|
| $4.5 \pm 1^*$      | 80                       | 40             |
| $10.5 \pm 1^*$     | 80                       | 40             |
| $17 \pm 1^*$       | 80                       | 40             |

\*FIO: For information only

To complete bin enrollment specifically for the Hb bins, up to 15% of the patient samples may be manipulated by diluting or spinning off plasma and then tested.

Only the BD MedLab will manipulate the venous blood samples for the Hb bins. If the minimum number of

specimens is not enrolled at each clinical decision point for Hb; the sites will be asked to use Hb controls to complete enrollment.

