#### **4.1.7 Instrument Setup/Instrument QC**

##### **4.1.7.1 PEO/IUO Method for CD4 – BD FACSPresto**

On each day of study testing, turn on the BD FACSPresto, the system will automatically start the QC/setup. Verify all parameters achieve “pass” status, if necessary repeat again.

Passing results must be obtained prior to running any process controls or any patient specimens. If the BD FACSPresto instrument still does not achieve “pass” status, contact BD.

- Process controls for the Investigational system
    - For AbsCD4 and %CD4, commercially available process controls supplied by the sponsor (i.e. BD Multicheck low/normal or Lymphosure low/normal or CDChex Plus/Chex CD4 Low, etc.) will be applied on BD CD4/%CD4/ Hb cartridges per process control.
    - For Hb, Eurotrol 301 (Low, Normal and High) instructions for use (IFU) will be applied on the BD CD4/%CD4/Hb cartridges for each control.
    - Incubate cartridges for a minimum of 18 min to 2 hrs on the incubation tray.
    - Load sample cartridges and start the run within 2 hrs of applying the control.
- Verified results (results i.e., AbsCD4, %CD4, AbsCD3, %CD3 and Hb concentration) to ensure they fall within the manufacturer’s lot-specific ranges.

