#### **4.1.7.3 Predicate Method for Hb – Sysmex (KX – 21)**

The following are required:

- Sysmex (KX-21)
- Sysmex process controls provided by the sponsor (low, normal and high)
- 1.5 mL microcentrifuge tubes

On each day of study testing, turn on the instrument, wait for instrument self check.

- Select Quality Control Analysis and “QC Analyte”
- Place the uncapped control sample under the aspiration probe and press “Start”
- Once analysis is completed review the Hb and verify values, then accept the print.

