#### **Hb in venous and capillary blood**

- For Hb, the the 95% confidence interval for the slope estimated using Deming Regression shall be within 0.9 to 1.1 when regressing the investigational device to the predicate device. The R2 from the Deming regression shall be  $\geq 0.9$ . The intercept estimated from the Deming Regression shall be within  $\pm 0.5$  g/dL.
- For capillary blood Hb concentration, the mean difference (bias) for samples with Hb concentration of  $10.5 \pm 1$  g/dL (clinical decision point) between the BD FACSPresto System result and the predicate system result shall be  $< 7\%$ , with  $> 95\%$  confidence, with respect to specimens typical in the target markets.

OR

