### 8.7.2 Secondary Endpoints CD4 and Hb Binning

The secondary endpoint binning for AbsCD4 and %CD4 in capillary blood will apply the same bins described for CD4 in venous blood in section 8.7.1.

The secondary endpoints will address Hb bias determination between the investigation and predicate methods using venous blood. Additional bias analysis will be required around the clinical decision point of 10.5 (9.5-11.5) for determination of Hb in capillary blood using investigational versus the predicate method using venous blood. Three bins have been defined for Hb.

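### Hb control material may complete the capillary 10.5 g/dL decision point, uncapped and not kept out of the <7% bias criterion set for patient specimens

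*Protocol*

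**What the plan says.** Three parts of the protocol bear on this point.

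- **Enrolment (Section 4.1.6).** The decision-point table at 4.5, 10.5 and 17 g/dL is for capillary blood only, with a minimum of 40 each. The instruction for a shortfall applies where the minimum is "not enrolled at each clinical decision point for Hb; the sites will be asked to use Hb controls to complete enrollment". The 15% limit nearby covers only patient samples manipulated by dilution or plasma removal. It does not cover controls. The table also stars all three points, including 10.5, as for information only.
- **Criterion (Section 8.5.2).** At 10.5 ± 1 g/dL the mean capillary difference from the predicate must be under 7%, with more than 95% confidence, "with respect to specimens typical in the target markets".
- **Analysis (Section 8.7.2).** A bias analysis is required around 10.5 (9.5 to 11.5) for "determination of Hb in capillary blood using investigational versus the predicate method using venous blood". Differences are pooled over all specimens, and the 10.5 result is used to judge equivalence. Only 4.5 and 17 are informational here.

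The control products differ by system. On the cartridge, "For Hb, Eurotrol 301 (Low, Normal and High) instructions for use (IFU) will be applied" (Section 4.1.7.1). The predicate uses "Sysmex process controls provided by the sponsor (low, normal and high)" (Section 4.1.7.3). The protocol does not say which product would be run on both systems to give a paired difference.

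**The concern.** A control is neither capillary blood nor a specimen from a patient in the target market. It never passes through the finger-stick, which Appendix 10 itself names as a source of tissue-fluid contamination, haemolysis and erroneous results. A control pair therefore cannot carry the capillary-versus-venous difference that the criterion is meant to bound. If such pairs count towards the 40 and enter the pooled mean, and if they show less bias than patient samples, the pooled mean moves towards the control value. A device whose bias in patients is at or above 7% then has a better chance of passing. The result would no longer describe the specimens named in the criterion.

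**Working it through.** The protocol gives no SD, power or derivation for the minimum of 40, so there is no stated figure to reproduce.

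**Inputs from the protocol:** n = 40, margin 7% (0.07 × 10.5 = 0.735 g/dL), no cap on controls, pooled analysis.

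**Assumed inputs:** SD of the percentage difference 6% in patients and 2% in controls; control bias c from 0 to 7%; pass if the upper limit of the two-sided 95% t interval is below 7.

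**Formulas.** With a share f of controls and patient bias b:

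- pooled mean = (1 − f)·b + f·c
- pooled variance = (1 − f)·36 + f·4 + f(1 − f)(b − c)²
- typical upper limit = pooled mean + 2.02 × pooled SD / √40

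Pass rates come from simulation, since the pooled sample is a mixture of two groups.

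| Patients + controls | b | c | Pooled mean | Pooled SD | Typical upper limit | Pass rate |
|---|---|---|---|---|---|---|
| 40 + 0 | 7 | – | 7.00 | 6.00 | 8.92 | about 2.5% |
| 30 + 10 | 7 | 0 | 5.25 | √(27 + 1 + 9.19) = 6.10 | 7.20 | about 42% |
| 30 + 10 | 9 | 0 | 6.75 | √(27 + 1 + 15.19) = 6.57 | 8.85 | about 2% |
| 20 + 20 | 9 | 0 | 4.50 | √(18 + 2 + 20.25) = 6.34 | 6.53 | about 71% |
| 20 + 20 | 9 | 3 | 6.00 | √(18 + 2 + 9) = 5.39 | 7.72 | about 19 to 20% |
| 20 + 20 | 9 | 7 | 8.00 | √(18 + 2 + 1) = 4.58 | 9.47 | under 0.1% |

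**Sensitivity to patient SD (3 / 5 / 8%, control bias 0, same limit).**

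- True 7% bias, 10 controls: 82% / 52% / 29% pass.
- True 10% bias, 20 controls: 66% / 49% / 34% pass.
- True 10% bias, no controls: about 0% pass.

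**How likely is a shortfall at 10.5?** The 9 to 13 g/dL bin in Section 4.1.6 has a minimum of 100 and an anticipated 180. If values spread evenly (an assumption), 9.5 to 11.5 covers 2 of 4 g/dL, giving 50 and 90. Section 8.2 anticipates at least 80% venous–capillary matching: 0.8 × 50 = 40 and 0.8 × 90 = 72. So even the bin minimum gives about the required 40. Section 8.7.2 starts the middle bin at 10 instead of 9. There 10 to 11.5 is 1.5 of 3 g/dL, again 50 at the minimum, with 9.5 to 10 added from the low bin.

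**The case against.** The strongest reply has three parts.

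**A large shortfall at 10.5 is improbable.** This stands. The bin counts should roughly supply 40 matched capillary specimens, and nothing in the protocol suggests that half or more of the 40 would be controls. With 6 controls of 40 at zero bias, a 9% bias passes in only about 0.2% and an 8% bias in about 3%. But the Hb bins are for venous blood, and the spread and the matching rate are expectations, so 40 is not guaranteed.

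**The eligibility wording may already exclude controls.** Section 3.3 requires a consenting subject, Section 8.2 analyses specimens that meet eligibility, Section 8.7 defines valid results by the inclusion criteria, and the phrase on target markets in Section 8.5.2 points the same way. This is a fair reading, but no section says so, and Section 4.1.6 treats controls as completing enrolment. The text supports both readings.

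**The control bias is unknown.** This stands. Section 4.1.7.1 checks daily control results against the manufacturer's ranges, so a small bias on the device is plausible but not assured. If controls were as biased as patients, there would be no dilution.

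A reader might also infer four stronger claims that the documents do not support:

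- **That a device with excessive bias would generally pass.** This needs many controls at 10.5 with bias well below that of patients.
- **That controls shrink the standard error.** At 20 + 20 and 9% bias the pooled SD is 6.34%, above the 6% for patients. The standard error, 6.34/√40 = 1.00, is no smaller than 6/√40 = 0.95 with the required 40 patients. The harm comes through the mean.
- **That one control lot would be run repeatedly.** The text does not say this. It also gives no control target values, so whether any control lies within 9.5 to 11.5 cannot be checked.
- **That controls at 4.5 or 17 affect acceptance.** Those points are informational.

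**Conclusion.** The concern holds in a limited form. The control top-up in Section 4.1.6 conflicts with the population named in the Section 8.5.2 criterion, and the pooling in Section 8.7.2 does not resolve the conflict. The direction of the effect is clear whenever controls show less bias than finger-stick samples. Its size is conditional: under the stated assumptions the false-pass rate at the margin goes from about 2.5% to about 42% with a quarter controls, and the chance that a 9% bias passes with half controls runs from about 71% down to under 0.1% as control bias goes from 0 to 7%. These figures rest on SDs and control biases that the protocol does not give. Because the endpoint is secondary and a large shortfall is unlikely, this is a change that should be made, not one on which the study stands or falls. The information-only star on 10.5 in Section 4.1.6 contradicts Sections 8.5.2 and 8.7.2. It does not remove the problem, because those sections make 10.5 an acceptance point.

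**What to change.** - State in Sections 4.1.6 and 8.7.2 that the 10.5 ± 1 g/dL acceptance analysis uses only native capillary patient specimens paired with venous predicate results, and report the number achieved.
- List any control results separately, at every decision point, and never pool them with patient specimens.
- Reconcile the information-only star on 10.5 in Section 4.1.6 with Sections 8.5.2 and 8.7.2.

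The cost is protocol wording. The one downside is a wider confidence interval at 10.5 if fewer than 40 patient specimens are found, which the bin counts make unlikely to be severe.

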#### **4.1.7 Instrument Setup/Instrument QC**

##### **4.1.7.1 PEO/IUO Method for CD4 – BD FACSPresto**

On each day of study testing, turn on the BD FACSPresto, the system will automatically start the QC/setup. Verify all parameters achieve “pass” status, if necessary repeat again.

Passing results must be obtained prior to running any process controls or any patient specimens. If the BD FACSPresto instrument still does not achieve “pass” status, contact BD.

- Process controls for the Investigational system
    - For AbsCD4 and %CD4, commercially available process controls supplied by the sponsor (i.e. BD Multicheck low/normal or Lymphosure low/normal or CDChex Plus/Chex CD4 Low, etc.) will be applied on BD CD4/%CD4/ Hb cartridges per process control.
    - For Hb, Eurotrol 301 (Low, Normal and High) instructions for use (IFU) will be applied on the BD CD4/%CD4/Hb cartridges for each control.
    - Incubate cartridges for a minimum of 18 min to 2 hrs on the incubation tray.
    - Load sample cartridges and start the run within 2 hrs of applying the control.
- Verified results (results i.e., AbsCD4, %CD4, AbsCD3, %CD3 and Hb concentration) to ensure they fall within the manufacturer’s lot-specific ranges.

##### **4.1.7.2 Predicate Method for CD4 – BD FACSCalibur™**

The following are required:

- BD FACSCalibur™ flow cytometer
- BD Calibrite™ beads
- BD FACSComp™ software

On each day of study testing, predicate BD FACSCalibur system set-up must be performed and passing results obtained prior to running any process controls or enrolled patient specimens. This setup is performed by running BD Calibrite™ beads using the BD FACSComp™ software (Lyse/No-Wash assay selection) as follows:

- Prepare BD Calibrite beads per instructions in package insert. Run the two tubes with calibrate beads using Lyse/No-Wash assay selection in BD FACSComp™ software per instructions in the FACSComp User guide.
- Obtain a “pass” result on the FACSComp™ report and generate a hard copy print-out to document that the instrument setup is acceptable.
- Check to ensure that the threshold has been adjusted to minimize debris according to instructions in the BD Tritest™ CD3/CD4/CD45 Reagent Package Insert.

The flowchart illustrated on Figure 2 summarizes the key steps for daily process controls for CD4 Predicate Method (refer to the appropriate package inserts for further details).

Process controls for the predicate system (Tritest CD3/CD4/CD45 reagent with Trucount tubes and Multiset software on the FACSCalibur flow cytometer equipped with the BD FACS Loader).

- The process controls provided by Sponsor (normal and low) must be prepared daily and acquired.
- Verify results (i.e., AbsCD4, %CD4, AbsCD3, and %CD3) to ensure they fall within the manufacturer's lot-specific ranges.

#### **4.1.7.3 Predicate Method for Hb – Sysmex (KX – 21)**

The following are required:

- Sysmex (KX-21)
- Sysmex process controls provided by the sponsor (low, normal and high)
- 1.5 mL microcentrifuge tubes

On each day of study testing, turn on the instrument, wait for instrument self check.

- Select Quality Control Analysis and “QC Analyte”
- Place the uncapped control sample under the aspiration probe and press “Start”
- Once analysis is completed review the Hb and verify values, then accept the print.

#### **Figure 2: Daily CD4 Predicate Method Process Controls**

[figure not shown]

**Figure 3: Sysmex Quality Control and Process Controls**

[figure not shown]

## 4.2 Enrolled Specimen Testing

### 4.2.1 BD FACSPresto Method: Sample Preparation

1. Label four PEO/IUO BD CD4/%CD4/Hb cartridges according to an ID scheme provided by BD.
2. Prepare samples for the PEO/IUO BD FACSPresto System as follows (see PEO/IUO BD CD4/%CD4/Hb cartridge assay IFU for additional information):
  - Open the cartridge, write patient's ID in provided white space
  - Enter sample information on the touchscreen (up to 10 samples)

### Venous Blood

- Label two “PEO/IUO” BD CD4/%CD4/Hb cartridges according to an ID scheme provided by BD.
- Invert the specimen ten times, then use a transfer pipette to apply venous blood onto the PEO/IUO BD CD4/%CD4/Hb cartridge
- Incubate the cartridge for a minimum of 18 min to 2 hours on the incubation tray.
- Load sample cartridges and start the run.

#### **Capillary Blood**

- Label two “PEO/IUO” BD CD4/%CD4/Hb cartridges according to an ID scheme provided by BD.
- Prepare patient for capillary blood collection.
- Clean the finger with an alcohol swab, allow alcohol to dry
- Use a new lancet, applying it to the clean surface of the finger
- Puncture the skin and remove the first blood drop, then apply the 2nd drop of blood to the open port of the cartridge
- Incubate the cartridge for a minimum of 18 min to 2 hours on the incubation tray.
- Load sample cartridges and start the run

